**Fig. 3 Fig3:**
[figure not shown]
Schedule of enrollment, interventions, and assessments in the SURF study

During each cycle of sunitinib before and after randomization (every 6 weeks), data collected will include symptoms and biological abnormalities, toxicities according to NCI CTCAE version 4.0, data related to sunitinib (start date, end date, dosage, dose modification and date, monitoring of compliance), toxicities related to sunitinib with grades according to NCI CTCAE version 4.0, and evaluation of HRQoL.

Tumor assessments will be performed every 12 weeks with evaluation of the response by RECIST 1.1 criteria.

During follow-up, cancer treatments provided later (start and end dates, type of treatment, reasons motivating the choice of treatment), the vital status and death-related data (date and cause), and the date and mode of progression for patients who left the study for reasons other than progression will be collected.

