#### Treatment duration

Patients participate until sunitinib is permanently discontinued for toxicity reason, progression, or death related to renal cancer or not.

The duration of follow-up after discontinuation of sunitinib will be 2 years. All death-related data will be collected as part of the study.

All patients included in this study can leave the study at any time, without having to justify the reason.

Study discontinuation include:Subject’s request to stop study treatment (withdrawal of consent)Decision of the investigatorTermination of the study by the sponsorAdverse eventsNon-compliance with the protocolProtocol-defined disease progressionLost to follow-upDeath

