### Analyses of time-to-event data

The median duration of treatment and other survival rates will be estimated using the Kaplan-Meier method. Median survival will be described with their confidence intervals (one-sided statistical test of significance (*α* 5%)) in each of the arms.

Survival curves will be calculated by the Kaplan-Meier method and described using their medians and their 95% confidence intervals.

Multivariate Cox analysis will be conducted to identify factors potentially influencing survival.

All variables originally collected will be tested by univariate analysis. The variables with *P* ≤ 0.20 will be eligible in multivariate analysis.

No *P* value will be indicated, and the effect size of treatment will be assessed using the HR with its confidence interval.

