#### Analyses of safety

Analyses of toxicities will be performed on all randomized patients who received at least one dose of treatment and analyzed according to the treatment received. The toxicities will be graded according to the NCI CTCAE version 4.0 classification. All toxicities occurring after the first dose of drugs after randomization and after the inclusion will be described according to their grade. The time until toxicity grade 3–4 will be estimated using the Kaplan-Meier method.

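### The Kaplan-Meier curve for time to grade 3–4 toxicity, read as risk, overstates the proportion of patients affected, and by more in the arm with shorter treatment; a cumulative incidence estimate should stand beside it

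*Protocol article*

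**What the plan says.** The section Analyses of safety sets the population: "Analyses of toxicities will be performed on all randomized patients who received at least one dose of treatment and analyzed according to the treatment received". It plans a description by grade: "All toxicities occurring after the first dose of drugs after randomization and after the inclusion will be described according to their grade". For the time to a severe event it names one method: "The time until toxicity grade 3–4 will be estimated using the Kaplan-Meier method". It gives no censoring rule and does not make death or stopping part of the event.

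Three other places decide who can still be observed to have a toxicity:

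- Treatment duration: "Patients participate until sunitinib is permanently discontinued for toxicity reason, progression, or death related to renal cancer or not". The same section adds: "The duration of follow-up after discontinuation of sunitinib will be 2 years".
- Clinical measures, during treatment: "During each cycle of sunitinib before and after randomization (every 6 weeks), data collected will include symptoms and biological abnormalities". Graded toxicities belong to this per-cycle list.
- Clinical measures, after treatment: the list covers later cancer treatments, "the vital status and death-related data (date and cause), and the date and mode of progression for patients who left the study" without having progressed. Toxicity is not on it.

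The Study design section gives, as the main hypothesis, that schedule 2/1 maintains efficacy with less toxicity. The Abstract gives the expected gain in median duration of treatment (DOT) as 6 to 8.5 months.

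**The concern.** Kaplan-Meier assumes that a censored patient would go on to have the event at the same rate as those still at risk. A patient who has died cannot. A patient who has stopped sunitinib for good is no longer exposed, and on the listed data collection is no longer observed for toxicity. Both are competing events. With them treated as censoring, 1−KM estimates what would happen if nobody died or stopped, not the share of patients who experience a grade 3–4 toxicity. Stopping is also unlikely to be independent of toxicity: a patient who stops for a lower-grade toxicity is censored because of poor tolerance.

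The distortion differs between the arms because time on treatment is expected to differ. Lower toxicity on schedule 2/1 is part of the main hypothesis, and the Discussion offers the results as support for routine use, so the absolute risk by arm is a figure clinicians will want to quote.

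**Working it through.** The article gives no figure for time to grade 3–4 toxicity, so there is none to reproduce. The check is an illustration with constant hazards.

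**Inputs**
- Competing hazard *d*, from the stated DOT medians: ln 2 / 6 = 0.1155 per month (arm 4/2) and ln 2 / 8.5 = 0.0815 per month (arm 2/1). DOT runs from sunitinib initiation; here it stands in for time from randomisation.
- Toxicity hazard *h*: not given, so assumed at 0.04, 0.06 and 0.08 per month.
- Horizon: 12 months.

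**Formulas**
- 1−KM(12) = 1 − exp(−12*h*)
- Cumulative incidence(12) = *h*/(*h*+*d*) × [1 − exp(−12(*h*+*d*))]

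**Equal toxicity hazard in both arms, *h* = 0.06**
- 1−KM = 1 − exp(−0.72) = 51.3% in both arms.
- Arm 4/2: 0.06/0.1755 × (1 − exp(−2.106)) = 0.3418 × 0.8783 = 30.0%.
- Arm 2/1: 0.06/0.1415 × (1 − exp(−1.699)) = 0.4239 × 0.8171 = 34.6%.

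| *h* per month | 1−KM, both arms | Incidence, 4/2 | Incidence, 2/1 | Excess, 4/2 | Excess, 2/1 |
|---|---|---|---|---|---|
| 0.04 | 38.1% | 21.7% | 25.3% | 16.4 points | 12.9 points |
| 0.06 | 51.3% | 30.0% | 34.6% | 21.3 points | 16.7 points |
| 0.08 | 61.7% | 37.0% | 42.4% | 24.7 points | 19.3 points |

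The excess is larger in arm 4/2 on every row. Kaplan-Meier shows no arm difference, while the proportions affected differ by 3.5 to 5.4 points, with arm 2/1 the higher. A simulation of 200,000 patients per arm, with *h* set so that 1−KM is 50% at 12 months, returned incidences of 29.2% and 33.7%, in agreement with the formula.

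**The trial's own hypothesis: 2/1 less toxic and longer on drug.** Take *h* = 0.06 in arm 4/2 and a hazard ratio of 0.7, so *h* = 0.042 in arm 2/1.
- 1−KM: 51.3% against 39.6%, a difference of 11.7 points.
- Incidence: 30.0% against 0.042/0.1235 × (1 − exp(−1.483)) = 26.3%, a difference of 3.7 points.

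At a hazard ratio of 0.83 the 12-month incidences are equal to within 0.1 point (30.0% and 30.1%), while 1−KM still separates the arms by 6.3 points.

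**Sensitivity, *h* = 0.06**
- Only death competes, assumed median survival 24 or 36 months: incidence 44.3% or 46.5%, an excess of 7.1 or 4.9 points.
- Shorter medians after randomisation, assumed 3 and 5.5 months: incidence 20.0% and 28.8%, so the excess widens.
- Part of stopping follows a grade 3–4 toxicity and so does not compete. If 28% of stops are removed on that ground (an assumption), *d* falls to 72% of its value, incidence becomes 34.4% and 38.4%, and the excess 17 and 13 points.

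**The case against.** Four arguments stand against the point.

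1. **No passage says that patients are censored when sunitinib stops.** The article plans two years of follow-up after discontinuation, and a full protocol or analysis plan may set the rule. This stands in part. Censoring at stop is an inference from the per-cycle collection and from the absence of toxicity in the follow-up list, and the larger gaps rest on it. The narrower part does not: with Kaplan-Meier and toxicity alone as the event, a toxicity-free death has nowhere to go but censoring. The time to quality-of-life deterioration, by contrast, counts death as an event.

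2. **Kaplan-Meier and cumulative incidence answer different questions.** Kaplan-Meier describes the rate while on treatment, given independent censoring. Cumulative incidence describes absolute risk, and it rises simply because patients stay on drug longer. This stands, and it is why Kaplan-Meier should be kept. A reader might infer that the curve hides differences between the arms. That is true only in some settings, such as equal hazards; under the trial's own hypothesis it shows the larger difference.

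3. **The competing hazard is too large**, because toxicity is itself a listed reason for stopping. This stands as a caution on size, as the last sensitivity line shows. A reader might also suppose that most stops are for progression; the article does not say so.

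4. **The curve is secondary and descriptive, no P value is planned, and counts by grade will be reported.** This lowers the stakes. Counts by grade do not, however, give the risk by a stated time.

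A reader might extend the point to time to randomisation, because the article says that "other survival rates will be estimated using the Kaplan-Meier method". That sentence does not name the endpoint, which is defined as a delay between two dates, so the documents do not support the extension.

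**Conclusion.** The point holds in a limited form. As the only time-to-event summary of severe toxicity, 1−KM overstates the proportion of patients affected, by more in the arm with shorter treatment. Read as risk, it distorts the arm comparison in a direction that depends on the hazards.

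Under the assumed hazards, with all stopping treated as competing, the 12-month excess is about 16 to 25 points in arm 4/2 and 13 to 19 points in arm 2/1. It falls to about 5 to 7 points (at 0.06 per month) if death alone competes. These figures rest on constant hazards, an assumed toxicity rate, DOT medians measured from initiation, and the inference that observation of toxicity ends when sunitinib stops. They illustrate the size and are not forecasts. The documents do not show that Kaplan-Meier is invalid for the on-treatment rate or that it must be replaced. This is a cheap improvement to a secondary safety analysis.

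**What to change.** In Analyses of safety, after the sentence on Kaplan-Meier, add: *The time from randomisation to first grade 3–4 toxicity will also be summarised by arm with the Aalen-Johansen cumulative incidence function, with permanent discontinuation of sunitinib and death, each without prior grade 3–4 toxicity, as competing events.* State the censoring rule for the Kaplan-Meier curve, and keep that curve or a cause-specific hazard ratio alongside, labelled as the on-treatment rate.

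The cost is a sentence or two of wording and a little programming. No new data are needed: toxicity, treatment end dates and deaths are already collected. The downside is that two summaries must be presented and explained together, and they may differ visibly.

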### Study duration

Up to 20 French sites will be opened for this study to achieve a total of 248 randomized patients (124 patients in each arm).

The main objective of this study is to estimate the DOT by sunitinib according to the administration regimen. The final analysis of the DOT will take place after 112 events. The total duration of the study (between the first inclusion and the final analysis) is estimated to be 60 months.

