### Statistics and data analysis

#### Sample size

The main objective of this randomized phase II trial is to evaluate the median DOT in each arm.

TThe following hypotheses will be tested: H0 (null hypothesis of inefficiency): median DOT of 6 months [15, 16] and H1 (alternative efficiency hypothesis): median DOT of 8.5 months. A Brookmeyer-Crowley type of test will be used to estimate the median. With a one-sided statistical test of significance (*α* 5%) and a power of 80%, it will be required to include 112 patients in each arm for 24 months with at least 12 months of follow-up.

The approximate upper critical value to reject H0 is 7.66 months. The number of patients is increased by 10% to take account of the potential progression or treatment discontinuation by patients before randomization and patients lost to follow-up. It will therefore be necessary to include 248 patients.

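### The final duration-of-treatment analysis is set at 112 events without saying total or per arm; taken literally as a total, it falls before recruitment ends and before the follow-up behind the 80% power

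*Protocol article*

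**What the plan says.** Three statements in the protocol article bear on when the primary endpoint is analysed.

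- **Sample size:** "it will be required to include 112 patients in each arm for 24 months with at least 12 months of follow-up". This supports a one-sided 5% test with 80% power of "H0 (null hypothesis of inefficiency): median DOT of 6 months" against "H1 (alternative efficiency hypothesis): median DOT of 8.5 months". The method is given as: "A Brookmeyer-Crowley type of test will be used to estimate the median". The earliest analysis consistent with this design is month 24 + 12 = 36.
- **Study duration, trigger:** "The final analysis of the DOT will take place after 112 events". The sentence carries no per-arm qualifier, although the same section gives the patient number both as a total (248) and per arm (124).
- **Study duration, calendar:** the "total duration of the study (between the first inclusion and the final analysis) is estimated to be 60 months".

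The Primary endpoint section counts DOT from sunitinib initiation. The Trial status section gives first enrolment in March 2016 and expected completion of recruitment in March 2018, which agrees with 24 months of accrual.

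**The concern.** The number 112 appears twice with different meanings: patients per arm in the power calculation, and events at the final analysis. The article does not link the two. A team that follows the Study duration sentence as written would count events over both arms and analyse at the 112th.

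At stake is the timing of the primary analysis in an open-label trial. If the literal count governs, the analysis comes while patients are still being included, the estimate around the median rests on short follow-up, and the stated power no longer applies. If the sentence stays ambiguous, the analysis time could be settled after open-label data have been seen.

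**Working it through.** **Inputs from the article.** One-sided 5%; medians 6 and 8.5 months; 112 per arm (224), raised to 124 per arm (248); accrual 24 months; minimum follow-up 12 months; 1:1 allocation; DOT from sunitinib initiation.

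**Assumptions not in the article.** Exponential DOT, uniform accrual, and every analysed patient counted from inclusion, with the lag to randomisation ignored. Both 224 and 248 patients are shown, because the article inflates for losses before randomisation but also plans 248 randomised.

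**1. Reproducing the stated power.** With at least 12 months of follow-up, survival at 6 months is estimated without censoring. Under a median of 8.5 months, S(6) = 2^(-6/8.5) = 0.613. The standard error with 112 patients is sqrt(0.613 × 0.387 / 112) = 0.046. Then (0.613 - 0.5)/0.046 - 1.645 ≈ 0.81, which gives power of about 79%. A simulation of the same test at month 36 (6,000 runs, Kaplan-Meier estimate at 6 months, Greenwood standard error) gives 79.4%. Closed-form variants need between 96.5 and 118.8 patients per arm, and the log-log version needs 115.3. The 80% is therefore reproduced closely and the 112 approximately. The stated critical value of 7.66 months is not matched exactly (7.51 on the log scale), but nothing below depends on it.

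**2. Events that the design implies.** With λ = ln 2 / median (0.1155 and 0.0815 per month), the probability of an event by calendar month t is

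- for t ≤ 24: [t - (1 - e^(-λt))/λ] / 24
- for t > 24: 1 - [e^(-λ(t-24)) - e^(-λt)] / (24λ)

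At month 36 this is 0.915 (median 6) and 0.835 (median 8.5).

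- 224 patients: 102.5 + 93.5 = 196 events
- 248 patients: 113.5 + 103.6 = 217 events

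**3. The trigger read as a total.** Solving for 112 events over both arms:

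| Patients | Medians | Month of 112th event | Included by then |
|---|---|---|---|
| 224 | 6 and 6 | 19.8 | 185 |
| 224 | 6 and 8.5 | 21.0 | 196 |
| 224 | 8.5 and 8.5 | 22.3 | 208 |
| 248 | 6 and 6 | 18.5 | 191 |
| 248 | 6 and 8.5 | 19.6 | 203 |
| 248 | 8.5 and 8.5 | 20.9 | 216 |

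Under 6 and 8.5 months, about 51 of the 112 events are in the experimental arm, and the trigger came before month 24 in more than 99.9% of simulated trials. At month 21.0 only patients included before month 9.0 could have 12 months of follow-up, which is 9/24 = 37.5% of the planned number. Slower accrual does not remove the problem: with 248 patients over 36 or 48 months, the 112th event is at month 25.7 or 31.6, still before accrual ends.

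**4. Power at that point (experimental arm, simulated).**

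| Patients per arm | Scale | Month 36 | At 112 total events |
|---|---|---|---|
| 112 | plain | 79.4% | 66.8% |
| 112 | log-log | 73.3% | 62.7% |
| 124 | plain | 80.1% | 68.4% |
| 124 | log-log | 80.1% | 65.1% |

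**5. The trigger read as per arm.** With 124 per arm, 112 events are expected at month 34.8 (median 6) and month 42.5 (median 8.5). This requires 112/124 = 90% of the arm to have stopped treatment. With only 112 patients in an arm it would require all of them.

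**6. The 60 months.** With 24 months of accrual, about 123 of 124 (median 6) and 121 of 124 (median 8.5) would have had the event by month 60. Neither reading of 112 events therefore leads to month 60. The per-arm reading gets there (59.7 months, median 8.5) only if accrual takes 48 months, against the 24 stated.

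**The case against.** The strongest defence has three parts.

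- **Per arm may be meant.** The Sample size figure of 112 is a per-arm figure. With 124 per arm the slower arm would govern, at month 42.5, which is 18.5 months after accrual ends. If both medians were 6 months, the count would come only about one month before month 36. This stands: the per-arm reading is broadly compatible with the Sample size section. The text does not say it, however.
- **The count may be a floor.** An analysis at month 36 is also one that takes place after 112 events, so the follow-up condition and the event count can both be met. The 60-month estimate also suggests that nobody foresaw an analysis near month 21. This stands as a possible intention. But a floor that is passed some 15 months before the analysis does not fix its date, and the sentence is worded as the trigger.
- **The 60 months may refer to another analysis.** The section names the final DOT analysis in one sentence and a final analysis of the study in the next. The second could be the end-of-study analysis, after the 2-year follow-up that the Treatment duration section sets: 24 + 12 + 24 = 60. The article does not give this sum, but it cannot be excluded.

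A reader might infer that the plan contradicts itself on every reading, or that a per-arm count could never be reached. The document does not support either. The per-arm timing fits the design, and the count becomes unreachable without a full set of events only if all 12 spare patients in an arm are lost.

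**Conclusion.** The point holds as a badly fixed analysis trigger. The count is unlabelled, repeats a patient number, and is not derived from the design. Taken literally as a total, it brings the primary analysis to about month 20 to 21 instead of month 36 or later, with 112 events where the design implies about 196 to 217. It costs roughly 12 percentage points of power in the experimental arm on the plain scale (about 79-80% down to about 67-68%). Taken per arm, it lands at about months 35 to 42.5 and does little harm to the design, but the 60 months remain unexplained.

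The timings and power rest on exponential DOT and uniform accrual, which are assumptions of this check and not of the article. The power loss applies only if the literal total is used and the 12-month follow-up condition is not also enforced. The article does not show that the sponsor intends such an early analysis; it shows only that the wording permits one.

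**What to change.** Replace the trigger sentence in the Study duration section with one of the following:

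- a time-based rule that matches the Sample size section: the final DOT analysis takes place once the last patient to be randomised has at least 12 months of follow-up, counted from sunitinib initiation as DOT is; or
- an event count derived from the design and labelled total or per arm. Under the assumptions above, about 196 (224 patients) to 217 (248 patients) total events are expected at month 36.

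Then reconcile the 60 months with the chosen rule, and say whether it refers to the DOT analysis or to the end-of-study analysis. If 112 per arm was meant, say so and state what happens if an arm does not reach it.

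The cost is one or two sentences, and an analysis later than the literal 112-event reading would give. The sample size does not change.

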## Discussion

At the time this manuscript was written, 80 patients have been included in the SURF trial, which makes it the largest prospective cohort of patients assessing the question of alternative schedule 2/1 of sunitinib. In comparison to the current available data, this trial will be able to provide more robust data about an alternative schedule of sunitinib based on an academic study.

The SURF trial is asking a pragmatic question adapted to the current practice: what is the best way to adapt sunitinib when side effects occur? In the SURF trial, randomization does not occur at the start of sunitinib but when a dose modification is required. The decision to randomize the patient is based on the choice of the physician. The purpose of the SURF trial is to bring robust prospective data of efficacy and side effects that can sustain the use of alternative schedule 2/1 in clinical routine practice. Furthermore, HRQoL data evaluated by the EORTC QLQ-C30 questionnaire will bring patient perspective on the alternative schedule.

One of the limitations of this design is a potential loss of power depending on the number of patients who may leave the study before randomization. We estimated that 10% of the patients could be lost between the initiation of the treatment and a potential randomization.

Recently, the FDA [17] approved sunitinib in an adjuvant setting for high-risk patients following the results of the S-TRAC trial, showing that sunitinib improved PFS in high-risk patients [18]. In this trial, patients started sunitinib at 50 mg with schedule 4/2. When toxicity occurred, dose interruptions or dose reductions to 37.5 mg per day were allowed, depending on the type and severity of the toxicity. An alternative schedule was not allowed. In the sunitinib arm, 48.8% of patients had grade III adverse events and 12.1% grade IV adverse events. Furthermore concerning HRQoL, on most QLQ-C30 subscales, patients in the sunitinib group had lower scores than those in the placebo group. Dose reductions and interruptions because of adverse events occurred in 34.3% and 46.4%, respectively, of the patients in the sunitinib group, and treatment discontinuations owing to adverse events occurred in 86 patients (28.1%) in the sunitinib group. In this setting, improving the management of side effects and maintaining HRQoL will be a high-priority topic.

Therefore, the results of the SURF trial will bring useful data on how to deal with sunitinib administration in case of toxicity, for clinicians dealing with patients having renal cell carcinoma at various stages of the disease.

